**Methods/Design:**

Twenty-one schools from Ciudad Real and Cuenca, Spain, were randomized to intervention and control groups. In the first academic year, children in the third grade of preschool and the first grade of primary school in the intervention group received the Movi-Kids intervention. In the second academic year, schools were crossed over to the other group. The intervention included children, parents and teachers, and the school environment, and consisted of: (i) three hour-long sessions of recreational non-competitive physical activity after school, weekly, (ii) educational materials for parents and teachers addressing sedentary lifestyle risks and (iii) playground modifications to promote physical activity during breaks. Primary outcome measures of this study were academic achievement (intelligence, cognition, memory, attention and perception), assessed by the Battery of General and Differential Aptitudes, and adiposity measures (body mass index, waist circumference, triceps skinfold thickness and body fat percentage). Secondary outcome measures were: attention deficit hyperactivity disorder risk, motor skills, health-related quality of life and sleep quality. These variables will all be measured in both groups at baseline and at the end of the first and second academic years.

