### Study variables and measurements

Baseline and post-intervention outcome variables were measured in both the control and intervention groups three times, at the beginning and end of the first academic year (in September 2013 and June 2014), and at the end of the second academic year (in June 2015). Table 1 provides an overview of all variables measured. Anthropometry (weight, height, body mass index, waist circumference, triceps skinfold thickness, percentage of body fat and fat-free mass) was performed in standardized conditions, as extensively described in the MOVI-2 protocol [37].

**Table 1 Tab1:** Study variables

Type of variable	Specific variables
Primary endpoint measures	Anthropometry: weight, height, body mass index, waist circumference, triceps skinfold thickness, percentage of body fat and fat-free mass by bioelectrical impedance analysis
	Academic achievement
Secondary endpoint measures	Attention deficit hyperactivity disorder risk: parents’ and teachers’ report using the Attention Deficit Hyperactivity Disorder Rating Scale-IV
	Motor skills: fine motor skills, throws and catches, and balance (static and dynamic), assessed by the Movement Assessment Battery for Children
	Health-related quality of life: children’s (by interview) and parents’ (self-administered) report, using the Kiddy-Kindl Questionnaire
	Sleep quality: parents’ report using the Children’s Sleep Habits Questionnaire, accelerometers, children’s sleep diary
Other endpoint measures	Physical activity: parents’ report by the Netherlands Physical Activity Questionnaire, accelerometers
Potential confounding factors	Age
	Sex
	Birthweight
	Breastfeeding: breastfeeding, formula feeding or both (mixed feeding)
	Food consumption: parents’ report, using the Children’s Eating Habits Questionnaire
	Family socio-economic status: education, occupation and socio-economic status index
	Area (urban or rural)
	Origin (native or foreign)

To minimize interobserver variability, the measurements were carried out in the school by trained investigators.

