### Study intervention

The design of Movi-Kids is based on the social ecological model [50], a theoretical model of behaviour change in which behaviour is understood as the interaction between the physical and social environment. The Movi-Kids programme is a multidimensional intervention aimed at influencing individuals (children, families and teachers) and the environment (including some changes in the physical structure of the playground).

The intervention was applied in the intervention group over two full academic years, and was implemented at three levels:Children participated in an optional extracurricular, play-based, non-competitive physical activity programme (Movi-Kids), adapted to their levels of motor competence (from 4 to 7 years old). The aim of this programme was to increase the weekly physical activity time through three 60 min sessions per week using school facilities. In addition, the Movi-Kids programme included basic sports games, playground games, dance and other activities focused on developing motor skills. At the end of the first year, approximately 90 sessions had been carried out in each school.Parents and teachers included in the intervention group were involved in activities to promote active lifestyles in their children. These activities included: (a) use of reinforcement tools that had demonstrated their utility in improving parents’ and teachers’ compliance and involvement in the programme (e.g., a refrigerator magnet with recommendations for physical activity for children), (b) answering a satisfaction-with-the-programme questionnaire, and (c) access to a blog (http://movi3kids.blogspot.com.es/) where parents could observe their children’s progress, read news regarding reinforcing healthy lifestyles, and ask questions of or make complaints to the research team.Finally, environmental interventions were conducted in the playground. Fixed (a balance circuit and panels with incentives to be physically active during break time) and mobile equipment (tyres of different colours and sizes) were put in the playgrounds to encourage children to be more active during playtime.

The standard physical education curriculum (1 hour per week of psychomotor activities to third-grade preschoolers and 2 hours per week of physical education to first-grade primary schoolers with physical activity levels at low-to-moderate intensity) was applied in both the control and intervention schools because this is compulsory in Spain.

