Since this was a cluster-crossover trial, clusters (schools) were randomized to intervention and control groups, with outcomes measured after the first period (first academic year), and then, after a washout period (the summer holidays), clusters crossed over from control to intervention groups, and vice versa.

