### Statistical analysis

The sample size was estimated to be able to show differences between the control group and the intervention group of 2 % (alpha error, 0.05; statistical power, 0.80) in mean body fat at the end of the first year. The estimated sample size was 140 children per group; this figure was multiplied by an inflation factor for cluster-randomized trials [51], which was estimated at 1.1264 using measurements from previous studies in body mass index [52]. To examine subgroup differences (e.g., sex, age, ADHD or socio-economic status) under the same conditions, and estimating a 15 % dropout rate, the minimal sample size was estimated at 1600 children (800 per group).

The statistical analysis will be carried out in two phases. In the first, we will verify that the randomization was effective in creating two comparable groups, examining the differences between the control and intervention groups in mean body fat and academic achievement. After that, we will identify outliers and extreme values, and their trustworthiness. Finally, we will check the adjustment of the variables to the normal distribution by using the Kolmogorov–Smirnov test and graphical procedures (normal probability plot).

In the second phase, we will assess the change between the intermediate and final evaluation variables in the first and second years of the study. Mixed regression models [53] will be estimated using each outcome variable as a dependent variable at the end of the first and second years of the study. The different models will be adjusted for baseline values, age and school (cluster), and the interventions will be treated as fixed affects (1 = intervention group, 0 = control group).

The results will be expressed as absolute differences in change in variables between the baseline and the final measurements (confidence interval of 95 %). When the dependent variable is the prevalence of overweight or obesity, the odds ratio will be calculated, together with a 95 % confidence interval.

Because of the different patterns of weight and height, triceps skinfold thickness and body fat, the models will be separately implemented for boys and girls. A separate analysis will also be conducted for ADHD (with or without), socio-economic status, origin (native or foreign), area (urban or rural), and state-funded or private school.

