Analyses will be carried out taking into account the CONSORT norms for the publication of the cluster design studies [54], with an intention-to-treat perspective, with children maintained in the group to which they were originally assigned, regardless of the number of sessions they attended.

Results will be considered statistically significant at *P* < 0.05, and the analysis will be performed using the 9.1 version of the SAS statistical package [55]. Mixed generalized lineal models will be used, PROC GENMOD for dichotomous variables, and PROC MIXED for continuous variables.

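### The year-2 contrasts, as stated, do not cleanly estimate the intervention effect in this cluster crossover; the year-1 contrast does

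*Protocol article*

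**What the plan says.** **Design.** The abstract of the protocol article says: "In the second academic year, schools were crossed over to the other group". The Study intervention section agrees and names the washout: "after a washout period (the summer holidays), clusters crossed over from control to intervention groups, and vice versa". That same section also says: "The intervention was applied in the intervention group over two full academic years". This last statement does not fit a swap of arms.

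**Measurement times.** Study variables and measurements lists three assessments: September 2013, June 2014 and June 2015. No assessment is listed in September 2014, after the summer washout.

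**Analysis.** The Statistical analysis section plans mixed models for each outcome at the end of both years, adjusted for baseline, age and school, with a treatment indicator of 1 for intervention and 0 for control. On its later analysis phase it states: "we will assess the change between the intermediate and final evaluation variables in the first and second years of the study". The reporting rule is "The results will be expressed as absolute differences in change in variables between the baseline and the final measurements". The intention-to-treat sentence describes the analysis "with children maintained in the group to which they were originally assigned", however many sessions each child attended.

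**Target of the sample size.** The same section sizes the trial for a 2 % difference in mean body fat at the end of the first year. The Discussion concedes that carryover is possible and gives no size for it.

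**The concern.** The stated rules (one group indicator, original assignment, change from baseline to the end) suit two parallel arms. Here the arms swap. At June 2015 a comparison by original group sets schools treated first against schools treated second, not treated against untreated. The other named contrast, from June 2014 to June 2015, starts from a value that is already shifted by treatment in one of the two sequences. It therefore adds one sequence's gain to the other's loss of effect.

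At stake is the size, and under one reading the sign, of the second-year result for both primary domains (adiposity and academic achievement). This is not a complaint about omitted detail. The article states the coding, the contrasts and the analysis set, and those statements do not match the design it describes.

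**Working it through.** **Inputs.** From the article: the swap after year 1; measurements in September 2013, June 2014 and June 2015; the 1/0 coding; the two contrasts; and a planning difference of 2 % body fat, read here as 2 percentage points. Assumed: d = −2 (a benefit), and r, the share of the year-1 effect still present one year after stopping, from 0 to 1. Baselines and period effects are taken as equal across sequences, and the effect while treated as the same in both years.

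**The plan's own figure.** The 140 children per group follow from a difference of 2, a two-sided alpha of 0.05 (sidedness assumed) and power of 0.80 if the SD is about 5.97. The article states no SD, so this is a back-calculation and not an independent check. It concerns year 1 only.

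**Expected outcomes.** Sequence A is intervention then control; sequence B is control then intervention. The period effects p1 and p2 are common to both.

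- June 2014: A = p1 + d; B = p1
- June 2015: A = p2 + r·d; B = p2 + d

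**Contrasts.**

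- Year 1, A − B: d
- Baseline to June 2015, original group (A − B): r·d − d = (r−1)d
- June 2014 to June 2015, original group: (r·d − d) − (d − 0) = (r−2)d
- Coded by the arm in force in year 2 (B − A): (1−r)d and (2−r)d respectively

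**With d = −2:**

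| Contrast | r = 0 | r = 0.5 | r = 1 |
|---|---|---|---|
| Year 1 | −2 | −2 | −2 |
| Baseline to final, original group | +2 | +1 | 0 |
| Intermediate to final, original group | +4 | +3 | +2 |
| Baseline to final, arm in force | −2 | −1 | 0 |
| Intermediate to final, arm in force | −4 | −3 | −2 |

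Under original-group coding neither contrast equals d for any r from 0 to 1. Under arm-in-force coding the first equals d only at r = 0 and the second only at r = 1.

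**Simulation check, original-group coding.** Assumptions: 21 schools of 76 children, true effect −2, total SD about 6, 100 runs per value of r, school-clustered standard errors. Mean estimates at r = 0, 0.5 and 1:

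- June 2014 adjusted for baseline: −2.02, −2.00, −2.07
- June 2015 adjusted for baseline: +2.00, +1.01, −0.04
- Baseline-to-final change: +1.99, +1.02, −0.03
- Intermediate-to-final change: +4.01, +3.01, +2.02
- June 2015 adjusted for the June 2014 value: +3.60, +2.58, +1.57

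At r = 0 and 0.5 the reversed year-2 estimates were significant at 0.05 in 99–100 % of runs. Adjusting for the earlier value, as the article's models do, does not remove the problem.

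**A two-year model coded by exposure.** With a period term and no carryover term it estimates about the average of d and (1−r)d, which is (2−r)d/2: −2, −1.5 and −1 at r = 0, 0.5 and 1. It is unbiased only at r = 0.

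**The case against.** A reader might infer that the plan, followed as written, must report a beneficial programme as ineffective or harmful. The article does not support that as a certainty. It does not say that the year-2 indicator means the year-1 group. The abstract and the Study intervention section use the word group for the arm in force: "clusters crossed over from control to intervention groups, and vice versa". The intention-to-treat sentence goes on to mention session attendance, so it may concern only adherence; in a crossover, what is assigned is a sequence. On that reading baseline-to-final is (1−r)d, which is exactly d under the full washout the design presumes and does not reverse for any r from 0 to 1. This objection stands against a firm claim of reversal. It does not rescue the pair of contrasts: intermediate-to-final is then (2−r)d, twice the effect under that same full washout.

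A reader might also infer that the two years are fitted separately, so that the within-school comparison is lost. The article does not say so. A stacked model with a school effect is compatible with its text, and period or sequence terms may be left to an analysis plan not shown. Their absence is not part of this point.

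Finally, the powered comparison is at the end of year 1 and is untouched, so a real effect can still be shown there. That stands, and it limits the consequence to what is reported for year 2.

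**Conclusion.** The concern holds for the year-2 contrasts. As stated, they do not cleanly estimate the intervention effect. By original group, which is the literal intention-to-treat wording, a true effect of −2 appears as +2 to 0 (baseline to final) or +4 to +2 (intermediate to final). By the arm in force, it appears as −2 to 0 or −4 to −2. No value of r makes both contrasts correct under either coding, and no September 2014 measurement exists to serve as a second-period baseline.

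The sizes rest on an assumed r between 0 and 1, on d = −2 taken from the planning difference, and on equal period effects across sequences; the formulas do not depend on the value of d. The sign reversal further requires original-group coding in year 2, which the text permits but does not settle. The year-1 contrast is valid at every r, so the documents do not support a claim that the trial's main comparison is invalid. All of this takes the crossover as described; the statement that the intervention group was treated for two years conflicts with it and must be resolved.

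**What to change.** 1. Name the June 2014 outcome, adjusted for the September 2013 baseline and compared by randomized group, as the effect estimate.
2. Drop the baseline-to-final and intermediate-to-final group differences as effect estimates, or label them as comparisons of treatment sequences.
3. For any two-year estimate, code exposure by school and year and keep the randomized sequence as the intention-to-treat unit. Fit one model to the June 2014 and June 2015 outcomes with exposure, period, September 2013 baseline, age and randomization stratum, and random effects for school, school-by-year and child. Report it as secondary, stating that it assumes no carryover and otherwise estimates about (2−r)d/2.
4. Reconcile the sentence in Study intervention on treatment over both academic years with the crossover described in that section and in the abstract.

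The cost is wording and model code; no new data are needed. The price is a two-year estimate that carries an explicit no-carryover assumption, which the available measurement times cannot remove.

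### All outcome models are to be fitted separately by sex, and further analyses separately by subgroup, with no stated whole-sample primary estimate, sex term or interaction test

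*Protocol article*

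**What the plan says.** All of this stands in the Statistical analysis section of the protocol article.

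- **Model terms.** Mixed regression models are planned for each outcome, with the intervention as a fixed effect: "The different models will be adjusted for baseline values, age and school (cluster" is the stated adjustment. Sex is not listed, although Table 1 and the Confounding variables section name it a potential confounder.
- **Split by sex.** The last paragraph of the section says that "the models will be separately implemented for boys and girls". The reason given is anthropometric: "Because of the different patterns of weight and height, triceps skinfold thickness and body fat".
- **Other splits.** The next sentence reads "A separate analysis will also be conducted for ADHD (with or without), socio-economic status", and goes on to origin, area and state-funded versus private school. The word 'also' marks these as additional. The sex split has no such word and describes how the models themselves are run.
- **Target of the sample size.** The trial was sized to "show differences between the control group and the intervention group of 2" % in mean body fat at the end of the first year ("alpha error, 0.05; statistical power, 0.80"). The total was then raised to 1600 children so that differences between subgroups, sex among them, could be studied, and to allow for 15% dropout.

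No interaction or heterogeneity test is mentioned anywhere in the article, and one significance threshold of 0.05 applies to all results.

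**The concern.** The sample size and the aim in the Background both concern one contrast, programme against control in all the children. The analysis text commits only to estimates within each sex and within other subgroups. Three things follow.

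- **Precision.** An estimate within one sex uses about half the children. Different growth patterns in boys and girls are handled in a joint model by a sex term, without giving up the overall estimate.
- **Testing differences.** The plan wants to study how effects differ between subgroups. Separate fits give an effect and an interval in each subgroup but no test of the difference. If one sex reaches 0.05 and the other does not, that is weak evidence that the effects differ.
- **Scope of the reason.** The justification concerns body measurements. Academic achievement is the other primary outcome, and the split applies to it with no reason given.

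What is at stake is a clear single answer on each primary outcome, and the risk that a chance discrepancy is read as the programme working in one sex or subgroup only.

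**Working it through.** **Inputs from the article (Statistical analysis).** Difference 2 % in body fat, read as 2 percentage points; alpha 0.05 (two-sided assumed); power 0.80; 140 per group before inflation; inflation factor 1.1264; dropout 15%; 800 per group in the end.

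**Assumptions.** The SD is not given and is back-calculated. Boys and girls are equal in number, and their estimates are treated as independent.

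**Step 1, the plan's own figures.** From n = 2(1.96 + 0.842)² SD² / 2² = 140, the SD is 5.97. An SD of 5.9 gives 137 and 6.0 gives 142, so 140 is consistent with an SD of about 6. Then 140 × 1.1264 = 157.7, and 157.7 / 0.85 gives 186 per group. Keeping 80% power in each of two sexes needs 2 × 157.7 / 0.85 = 371 per group. No whole multiplier gives 800 (four subgroups give 742, five give 928), but 800 more than covers a split by sex at 2 points.

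**Step 2, standard errors.**
- Whole sample: effective n = 800 × 0.85 / 1.1264 = 603.7 per group; SE = 5.97 × √(2/603.7) = 0.344.
- One sex: effective n = 301.8 per group; SE = 5.97 × √(2/301.8) = 0.486.
- Ratio: 0.486 / 0.344 = √2 = 1.41.
- Detectable difference at 80% power (2.80 × SE): 0.96 points pooled, 1.36 points in one sex.

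The 1.41 keeps the same inflation factor for both fits. If the factor falls with the number of children per school, the ratio is √(2 × DE_sex / DE_all) with DE = 1 + (m − 1) × ICC. Here m = 680 / 10.5 = 64.8 for all children and 32.4 for one sex. Assumed ICCs of 0.002, 0.01 and 0.02 give ratios of 1.37, 1.27 and 1.20.

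**Step 3, same true effect d in both sexes.** Power = Φ(d/SE − 1.96). The chance that exactly one sex is significant is 2p(1 − p), where p is the power per sex.

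| d (points) | Power, pooled | Power, each sex | Exactly one sex significant |
|---|---|---|---|
| 2.0 | over 99% | 98% | 3% |
| 1.5 | 99% | 87% | 23% |
| 1.0 | 83% | 54% | 50% |
| 0.5 | 31% | 18% | 29% |

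**Step 4, larger clustering.** At d = 2 with a design effect of 2.0 instead of 1.1264, power per sex is 87% and the last column becomes 23%. With a design effect of 3.0 they are 71% and 41%.

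**Step 5, the interaction test.** SE = √2 × 0.486 = 0.688. Power for a 2-point difference between the sexes is Φ(2/0.688 − 1.96) = Φ(0.95) = 83%. For 1.5 points it is 59%, and for 1.0 point 31%.

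**The case against.** **The sample was enlarged for this purpose.** The total of 1600 was chosen with subgroups in mind, and the detectable difference of 1.36 points in one sex lies inside the 2-point target. This stands. At the planned effect and the plan's own inflation factor the loss is of little consequence.

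**Stratifying by sex is prespecified and reasoned.** It lets baseline slopes and variances differ between boys and girls. This stands for the anthropometric outcomes as a supporting analysis. It does not extend to academic achievement, and a joint model can include such terms.

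**A reader might infer that there will be no all-children estimate.** The article does not say so. It defines one intervention contrast before it introduces the split, and a full protocol or analysis plan, not shown, may contain a whole-sample model and interaction tests. What can be said is that the article states none, while it does state a split by sex.

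**A reader might infer that the type I error nearly doubles.** Two independent tests give 1 − 0.95² = 9.75%. That holds only if success in either sex counts as success, and the article has no such rule. Nor does it say that subgroup differences will be judged by comparing P values; it promises differences with 95% confidence intervals. Boys and girls also share schools, so the independence behind 9.75% is doubtful.

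**A reader might infer that the sexes will often disagree at the planned effect.** With 80% power per sex, exactly one would be significant in 2 × 0.8 × 0.2 = 32% of trials. The plan's own figures give about 98% power per sex and about 3%.

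**Conclusion.** The point holds as a weakness in the stated analysis, and it is cheap to correct. The article fixes separate fitting by sex for all outcome models, plus separate subgroup analyses. It names no whole-sample primary estimate, sex term or interaction test, and so does not match a sample size built on one overall difference or the aim of studying subgroup differences.

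The size depends on the true effect. The standard error within one sex is about 1.41 times the pooled one, or somewhat less if the cluster inflation shrinks with fewer children per school. At 2 points the practical harm for the sex split is small. For a common effect of 1.0 to 1.5 points, one sex alone would be significant in about 50% to 23% of trials. At 1.0 point, power is 54% per sex against 83% pooled.

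These figures rest on the back-calculated SD of 5.97, two-sided testing, 15% dropout, equal numbers of boys and girls, and independence between the sexes. Because the sexes share schools, the chances of disagreement are approximate.

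**What to change.** - Name the whole-sample model as the primary analysis for each outcome, academic achievement included, with sex added to baseline value, age and school.
- Add arm-by-sex and arm-by-subgroup interaction terms for ADHD, socio-economic status, origin, area and school type in whole-sample models.
- Report sex- and subgroup-specific effects with confidence intervals as secondary results.
- Claim a difference between subgroups only from the interaction.

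If a full protocol or analysis plan already has these, the article's wording should be brought into line with it.

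The cost is wording and a few model terms; no new data are needed. The downside is that interaction tests have lower power than tests within a subgroup: about 83% for a 2-point difference between the sexes under the plan's own inflation factor, against 98% for a 2-point effect within one sex. It falls to 59% for a 1.5-point difference. A non-significant interaction should therefore not be reported as proof of equal effects.

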## Methods/Design

### Study design and participants

A crossover randomized cluster trial was carried out, involving 21 schools located in as many municipalities in the provinces of Cuenca and Ciudad Real, in the Castilla-La Mancha region of Spain. All of them were state-funded schools except for two, which were private. In municipalities with more than one school, only one was selected for the study, to avoid contamination of the intervention. At first, 22 schools were invited, and only one of them refused to participate in the study, arguing that the study could mean excessive administrative overheads for the teachers. After the approval of school councils, the schools were randomly allocated using the statistical package StatsDirect to either the intervention or the control group; finally, the whole sample of schools was divided into three subgroups of randomization as follows: (i) nine public schools from Cuenca, (ii) ten public schools from Ciudad Real, and (iii) two private schools, one in the capital of each province (Fig. 1). All children belonging to the third grade of preschool and first grade of primary school (aged 4 to 7 years) were invited to participate.

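### The separate private-school analysis rests on two schools and leaves no school-level degrees of freedom for a standard error

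*Protocol article*

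**What the plan says.** Under Study design and participants, the article describes 21 schools as the clusters: "All of them were state-funded schools except for two, which were private". It then says that "the whole sample of schools was divided into three subgroups of randomization as follows". Two of these subgroups hold the state-funded schools, listed as "i) nine public schools from Cuenca, (ii) ten public schools from Ciudad Real"; the third consists of "two private schools, one in the capital of each province". How the two private schools were divided between the arms is not stated in the text, and the flow chart is not shown.

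Under Study intervention, after the summer break "clusters crossed over from control to intervention groups, and vice versa".

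Under Statistical analysis, mixed models are to be fitted "using each outcome variable as a dependent variable at the end of the first and second years of the study", and they are "adjusted for baseline values, age and school (cluster), and the interventions will be treated as fixed affects". Differences are to be given with 95 % confidence intervals and judged at P < 0.05. The last paragraph on the models adds separate analyses for several factors, ending with "area (urban or rural), and state-funded or private school". Nothing restricts the private-school part to description or says where its error term would come from.

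**The concern.** Schools were randomized, so the error of a treatment contrast has to include variation between schools. A separate private-school model has only two schools from which to learn that variation, and the treatment contrast already uses up the one comparison they offer. An interval printed from such a model would describe how children vary within schools and would leave out how schools differ from each other or drift from year to year.

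An ordinary difference between two schools could then be published as an intervention effect in private schools or, set beside the state-funded result, as evidence that the programme works differently by type of school.

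**Working it through.** **Counts.** 9 + 10 + 2 = 21, which agrees with the article. State-funded: 9 + 10 = 19. Private: 2.

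**Degrees of freedom in the private stratum**, working with school-by-year means:

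- *One school per arm, single-year model* (as the article describes). Two means; parameters are intercept and treatment. Residual df = 2 − 2 = 0. If school is entered as a fixed effect, the columns are intercept, school and treatment: 3 columns, rank 2, so treatment is aliased with school. If school is random, its variance cannot be estimated alongside treatment. As the two schools lie in different provinces, the contrast is also Cuenca against Ciudad Real.
- *One school per arm, both years pooled as a crossover.* Four means; columns for intercept, school, period and treatment have rank 4. Residual df = 4 − 4 = 0. School and province main effects drop out, because each school receives both conditions, but treatment is then the school-by-period contrast itself. The adjustment list in the article names no period term. Omitting it would give 4 − 3 = 1 df, but only by using the year-to-year change of growing children as the error term.
- *Both schools in the same arm.* Within a year there is no private-school contrast. Over two years the same four columns have rank 3, because treatment is aliased with period.

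**Size of the error if only child-level variation is used.** Take one school per arm, m children in each, a single-year comparison, and a two-sided normal test. The true variance of the difference is the child-level variance multiplied by 1 + (m − 1) × ICC. Hence

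true type I error = 2 × [1 − Φ(1.96 / √(1 + (m − 1) × ICC))].

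Inputs:

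- Cluster inflation factor 1.1264 (Statistical analysis; taken there from body mass index data).
- m is not given. Assumed 76, from 1600 / 21 = 76.2; 40 is also assumed, as a smaller case.
- ICC is not given. Equating 1 + (m − 1) × ICC with 1.1264 at m = 76.2 gives 0.1264 / 75.2 = 0.0017. The values 0.01, 0.02 and 0.05 are assumptions that show the range.

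| ICC | m = 76 | m = 40 |
|---|---|---|
| 0.0017 | 0.065 | 0.058 |
| 0.01 | 0.138 | 0.096 |
| 0.02 | 0.215 | 0.142 |
| 0.05 | 0.368 | 0.254 |

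Example, m = 76 and ICC = 0.02: 1 + 75 × 0.02 = 2.5; 1.96 / √2.5 = 1.24; two-sided tail 0.215.

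**The case against.** Five points can fairly be made for the plan.

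- *The crossover protects the comparison.* In part. A reader might infer that the private-school effect is wholly confounded with school and province whatever is done. The documents support that only for the single-year models. A pooled within-school contrast removes both main effects, but it does not supply degrees of freedom.
- *The split of one school per arm is not documented.* Correct. A randomization subgroup of two schools points to it, but the text does not say so. The conclusion does not depend on it, since the other allocation leaves no usable contrast either.
- *The inflation may be small.* This stands. At the ICC implied by the plan's own factor, type I error is 0.058 to 0.065, close to nominal. Adjustment for baseline should also reduce residual variation between schools. However, the private-school data cannot show whether the ICC is that low. Expressing the error in body-fat points would need a standard deviation that the article does not give.
- *The software might not return a false p-value.* A reader might infer that the mixed model is bound to set the school variance to zero and print an over-precise result. That depends on the random-effect specification and the degrees-of-freedom method, which are not given; the fit might equally yield no usable test. Neither outcome is informative.
- *Variance could be borrowed from the other 19 schools, and such detail belongs in an analysis plan.* Borrowing needs a joint model with an interaction term and the assumption that private and state-funded schools vary equally. The article announces a separate analysis, which most naturally means stratified models. The objection is to what is stated, not to a missing detail.

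**Conclusion.** The point holds for the private-school half of this subgroup analysis. With two private schools, no allocation and no pooling of years leaves a school-level degree of freedom once period is accounted for, so the contrast cannot have a valid standard error from those schools alone. This follows from the article's own counts and needs no assumed figure.

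The size of the resulting error does rest on assumptions: one school per arm, 76 children per school, and a child-level standard error. Type I error is then about 0.065 at an ICC of 0.0017 and 0.14 to 0.37 at ICCs of 0.01 to 0.05.

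A reader might go further and infer that the whole analysis by school type, or the trial's main result, is compromised. The documents do not support that. The 19 state-funded schools can be analysed, and the primary comparison uses all 21. School type is also not among the examples of subgroups named in the sample-size paragraph. This is a limited defect, worth correcting because the correction is easy.

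**What to change.** In the last paragraph on the models under Statistical analysis, withdraw inference for the private-school subgroup. State that the two private schools will be reported descriptively, as means by school and time point, with no p-value or confidence interval, and that no claim of effect modification by school type will be made. Keep the analysis of the 19 state-funded schools, which is already half of what is planned, and label it a sensitivity analysis. The main model needs no change.

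The cost is a sentence or two of text and the loss of a subgroup estimate that could not have had a valid standard error.
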